
### Data analysis plan

Cohorts will be compared by matching patients based on their propensity scores (PS) to be treated with acenocoumarol versus each of the four DOACs and versus warfarin in order to counteract the risk of selection bias when comparing the 5 different cohorts of OACs against the reference treatment cohort (acenocoumarol). This can be viewed as an attempt to emulate a randomized experiment (quasi-experimental study).

We consider that *propensity score matching* is of relevance in new RWD studies, and is more appropriate than other methods, such as *inverse probability of treatment weighting* (IPTW). After consulting the literature, matching cases by propensity score at the beginning of the study seems to be a more suitable epidemiological approach than first calculating a propensity score and assigning a weight to each case, before calculating the IPTW, unlike other publications on RWD in oral anticoagulation [10, 14, 15]. This strategy will help to control for selection bias by creating case-matched treatment groups that will be more comparable based on baseline patient characteristics.

A longitudinal registry will be created in a database that will later be imported with the Excel, R and Stata statistical packages together with the definitions of the variables described. The risk of events (effectiveness and safety) in patients treated with VKA and DOACs will be assessed.

Quantitative variables will be summarised as means and standard deviations, and in case of highly skewed distributions, as median and interquartile ranges (p25, p75). Frequency tables and percentages will be used for non-quantitative variables. Point estimates and 95% confidence intervals will be obtained for the different statistical analyses.

Contingency tables will be developed and the chi-square test, chi-square with continuity correction, and Fisher’s exact test (for 2x2 tables with small samples) will be applied to assess the relationship between two qualitative variables. In our analysis, parametric statistical tests will be used when variables fulfil the assumptions of normality and independence. Parametric tests are usually more powerful and sensitive when the data follow a normal distribution, allowing us to obtain more accurate and meaningful results. Non-parametric tests will be applied if the assumption of normality is not met.

Univariate survival analysis (for time-censored data) will be performed using Kaplan-Meier curves to represent the frequency of occurrence of different events or diseases over time and, where appropriate, in relation to different categories of a variable (age groups, sex, province, etc.) [18].

Survival probabilities, median and quartiles will be calculated, generating statistics and plotting survival functions for each study group.

The log-rank test will be used to test the equality of survival time distributions between different groups.

A preliminary univariate analysis will be performed to identify variables related to time-to-event occurrence (comparing event incidence density to person time to follow-up for different categories of variables).

To analyze this database, confounding variables identified in previous studies will be taken into account. Statistical analyses will include bivariate analysis (association between type of anticoagulant used and each of the other study variables); the Mantel-Haenszel test (analysis stratified by a third variable), as well as multivariate analysis.

A multivariate survival analysis will be performed using Cox proportional hazards or time-dependent Cox regression to control for the effect of confounding variables in the study. Cox regression will be used to create time-to-event models, considering both categorical and continuous predictor variables (covariates) as hypothetical predictors. Potential confounding variables include: age, sex, contacts with health service, comorbidities, concomitant medications, CHA2DS2-VASC and HAS-BLED scores, and previous ischemic and bleeding events.

Determination of the risk of outcomes among DOACs or warfarin versus acenocoumarol (reference) users will be obtained by calculating the specific instantaneous risk ratios for each comparison (Hazard Ratio) (HR) using multivariate Cox regression models. Adjusted survival curves will be used to represent how event risks will evolve over time after adjusting for different confounding variables.

A significance level of 0.15 will be used in preliminary univariate analysis to enable the selection of variables for inclusion in multivariate analysis. Once these variables have been selected, a multivariate analysis will be performed to select the final model. The analysis will be performed for both effectiveness and safety events. HRs and 95% confidence intervals (95% CIs) will be calculated for the selected variables once the application requirements have been validated.

The characteristics of the total study population and of each of the cohorts based on the first OAC used will be reported in the corresponding tables as percentages, means (standard deviation) or medians (interquartile range). Incidence rates will be calculated as the number of events divided by the corresponding denominator of person-time in follow-up.

Intention-to-treat analysis will be carried out by categorising each patient according to the first anticoagulant treatment they start taking in the study period, provided that they have not taken any other anticoagulant for at least 12 months previously (“washout period”) and regardless of any possible changes in type of anticoagulant or non-adherence that may occur in the follow-up period (Fig 3).

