### Population and setting

The study will be carried out in the region of Andalusia, where the Public Health System of Andalusia) (PHS-A) provides health coverage to a population of 8.4 million inhabitants.

The patients in the study will be those seen in consultations at any level of health care of the PHS-A (primary care and hospital) between January 2012 and December 2020 (Fig 1) who meet the following inclusion/exclusion criteria:

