### Outcome measures

The pre-specified effectiveness outcomes will be the incidence of new diagnosis among the following list: transient ischaemic attack, systemic embolism, pulmonary embolism, ischaemic stroke and all-cause mortality, as a combined effectiveness endpoint.

Safety outcomes will be the incidence of new diagnosis of major haemorrhages leading to hospital admission (gastrointestinal and intracranial haemorrhages). They will be considered as a combined safety endpoint. Post-traumatic bleeding will be excluded.

All effectiveness and safety events will be associated with their dates of onset and identified using the corresponding International Classification of Diseases (ICD-9 or ICD-10 codes) (S2 Table).

Time-to-event will be defined as the number of days elapsed from the date of initiation of treatment (dispensing at pharmacy) until the date of the event, death or the end of study period (December/2020).

The following independent variables will be analysed according to relevance and availability in PHS-A databases:

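### Kaplan-Meier and adjusted survival curves that stop at death will overstate the cumulative incidence of haemorrhage and of any non-fatal event shown on its own

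*Protocol article*

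**What the plan says.** Four statements in the protocol article combine on this point.

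- **Estimator.** The section Data analysis plan calls for "Kaplan-Meier curves to represent the frequency of occurrence of different events or diseases over time", together with survival probabilities, medians and quartiles for each study group.
- **Adjusted curves.** The same section says: "Adjusted survival curves will be used to represent how event risks will evolve over time".
- **Clock.** The section Outcome measures counts days from first dispensing "until the date of the event, death or the end of study period (December/2020".
- **Endpoints.** The safety endpoint is "major haemorrhages leading to hospital admission (gastrointestinal and intracranial haemorrhages", which does not include death. The effectiveness endpoint ends with "ischaemic stroke and all-cause mortality, as a combined effectiveness endpoint", so death is an event there.

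The plan applies the analysis to both effectiveness and safety. It does not mention competing risks or a cumulative incidence function.

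**The concern.** A patient who has died cannot later be admitted with a bleed. Kaplan-Meier with death censored assumes that this patient would have gone on to bleed at the same rate as the survivors. One minus Kaplan-Meier therefore describes a population in which nobody dies. The plan says that the curve shows how often events occur, and for haemorrhage it does not.

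What is at stake is absolute risk: the height of the bleeding curves and any difference that a reader takes off them. All-cause death is itself a study outcome, and the limitations section expects selection in the choice of anticoagulant, so mortality may differ between the drugs. The size of the error would then differ between curves that are meant to be compared. Propensity score matching reduces baseline differences in mortality, but it does not turn one minus Kaplan-Meier into a cumulative incidence.

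**Working it through.** **Inputs from the document.** The clock ends at event, death or December 2020. Patients are those seen "between January 2012 and December 2020", so follow-up is at most 9 years. It is about 8 if the 12-month washout must fall within data from 2012 onwards. The article states no bleeding rate, death rate or mean age, so there is no figure of the plan's own to reproduce.

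**Assumed inputs.** Constant hazards: a for the event and d for death without the event, with T the years of follow-up.

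**Formulas.**

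- One minus Kaplan-Meier, death censored: 1 − exp(−aT)
- Cumulative incidence, death competing: a/(a+d) × [1 − exp(−(a+d)T)]

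**Example.** With a = 0.015, d = 0.06 and T = 9:

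- 1 − exp(−0.135) = 12.6%
- 0.015/0.075 × [1 − exp(−0.675)] = 0.2 × 0.491 = 9.8%
- Ratio 12.6/9.8 = 1.29

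**Results for a = 1.5 per 100 person-years**

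| Years | 1 − KM | Cumulative incidence, d = 4 / 6 / 8 per 100 person-years | Relative excess |
|---|---|---|---|
| 1 | 1.49% | 1.46 / 1.45 / 1.43% | 2 / 3 / 4% |
| 3 | 4.4% | 4.1 / 4.0 / 3.9% | 6 / 9 / 12% |
| 5 | 7.2% | 6.6 / 6.3 / 6.0% | 10 / 16 / 21% |
| 9 | 12.6% | 10.7 / 9.8 / 9.1% (10.65, 9.82, 9.07) | 19 / 29 / 39% |

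**Wider range.** Over a = 1 to 3 and d = 1 to 10 per 100 person-years, the excess at 9 years runs from 0.4 to 7.8 percentage points, or 4% to 51% in relative terms.

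**Simulation.** 400,000 patients were simulated with a = 2 and d = 8 per 100 person-years and administrative censoring spread evenly over 0 to 9 years. At 8.9 years this gave 16.5% against 11.9%, close to the formula's 9-year values of 16.5% and 11.9%.

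**Differences between drugs at 9 years**

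- *Equal mortality* (d = 6), bleeding 1.5 against 2.0: the Kaplan-Meier difference is 16.5 − 12.6 = 3.8 points (before rounding). The true difference is 12.8 − 9.8 = 3.0 points. The curve shows too large a gap.
- *Equal bleeding* (a = 2), deaths 5 against 8: Kaplan-Meier gives 16.5% in both groups, a difference of zero. The true incidences are 13.4% and 11.9%, a difference of 1.5 points. The curve shows too small a gap.

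**Composite that includes death.** No death is censored, so one minus Kaplan-Meier and the cumulative incidence are the same quantity.

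**The case against.** The strongest reply is that the comparative results do not depend on these curves. The plan takes the drug effects from Cox hazard ratios and adds person-time rates. With death censored, both are valid cause-specific measures. So is the log-rank test ("The log-rank test will be used to test the equality of survival time distributions between different groups"), read as a test of cause-specific hazards. A reader might infer that the comparison of the drugs is biased as a whole; the document does not support that. It also commits to no absolute risk difference between drugs. All of this stands, and it confines the point to the curves and the absolute risks read from them.

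Further limits also stand:

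- A reader might extend the point to effectiveness as a whole. The defined effectiveness endpoint includes all-cause death and is unaffected. Separate thromboembolic curves are suggested only by the plan's general reference to different events, so that part is conditional on their being shown.
- A reader might infer that absolute differences between drugs are always too large. The second example above shows the opposite.
- A reader might take 9 years in an elderly cohort as typical. The article gives only a lower age limit of 40, and 9 years is reached only by the earliest entrants. Follow-up is shorter for drugs marketed later.
- Medians and quartiles matter little here: a 9-year figure of 12.6% does not reach even the first quartile.

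It can also be said that the coding of death is inferred, since the article lists when time stops and does not name death as censoring for haemorrhage. But a standard Kaplan-Meier curve offers only event or censoring, and death is not a haemorrhage event. The rule of counting the first recorded effectiveness or safety event does not change this. Nor is this merely a detail left to a fuller plan: the estimator and its stated purpose are both fixed here, and they do not fit each other.

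**Conclusion.** The point holds for the haemorrhage endpoint, and for any non-fatal thromboembolic component plotted separately. For these, one minus Kaplan-Meier and the adjusted survival curves will overstate actual cumulative incidence. The direction is certain as long as some patients die without the event while others are still followed.

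The size rests on assumed constant rates. At 1.5 bleeds and 4 to 8 deaths per 100 person-years, it is 10% to 21% at 5 years and 19% to 39% at the 9-year maximum. It is only 2% to 4% at 1 year, and about 4% at 9 years if mortality is 1 per 100 person-years. Absolute differences between drugs may be distorted in either direction. The hazard ratios, the log-rank test, the person-time rates and the death-including composite need no change on this account. The correction should be made, but it does not put the main comparative estimates in doubt.

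**What to change.** 1. For haemorrhage, and for any non-fatal component shown on its own, replace one minus Kaplan-Meier with the Aalen-Johansen cumulative incidence function, treating death as a competing event.
2. Derive the adjusted risk curves for these endpoints from two cause-specific Cox models, one for the event and one for death without the event.
3. Keep the cause-specific hazard ratio and the log-rank test, and report the hazard ratio for death beside them. Gray's test may be added, but it answers a different question and need not replace the log-rank test.
4. Keep Kaplan-Meier for all-cause death and for the effectiveness composite that includes death.

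Dates of death are already needed for the effectiveness endpoint, and the plan already names R and Stata, which cover these methods. The cost is one extra model for death per comparison, a few sentences in the plan, and somewhat lower reported absolute risks.

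### A univariate screen at 0.15 and a second selection step, not prior knowledge, decide which known confounders adjust the Cox hazard ratios

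*Protocol article*

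**What the plan says.** All of this is in the Data analysis plan section of the protocol article.

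- Prior knowledge is invoked: "confounding variables identified in previous studies will be taken into account". A list follows: "Potential confounding variables include: age, sex, contacts with health service, comorbidities, concomitant medications, CHA2DS2-VASC and HAS-BLED scores, and previous ischemic and bleeding events".
- The screen looks at the outcome: "A preliminary univariate analysis will be performed to identify variables related to time-to-event occurrence".
- The entry rule is numerical: "A significance level of 0.15 will be used in preliminary univariate analysis to enable the selection of variables for inclusion in multivariate analysis".
- A second step follows: "Once these variables have been selected, a multivariate analysis will be performed to select the final model".
- Reporting comes from that result: "HRs and 95% confidence intervals (95% CIs) will be calculated for the selected variables once the application requirements have been validated".
- The HRs for each direct anticoagulant or warfarin against acenocoumarol are obtained "using multivariate Cox regression models".

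No sentence keeps a listed confounder in the model whatever its p-value. The criterion of the second step is not stated. The same section also plans propensity score matching of acenocoumarol against each of the five other drugs.

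**The concern.** A confounder is related to both treatment and outcome. The univariate screen tests only the second relation, without adjustment, and its result depends on how many events there are. A variable that strongly drives drug choice can fail because few events lie behind it, or because another variable masks its marginal association. The plan therefore has the knowledge to fix an adjustment set and then lets a p-value override it.

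Two things are at stake. Omitted confounders leave bias in the treatment HR. In addition, a 95% interval computed as if the selected model had been fixed in advance ignores the uncertainty of the selection.

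**Working it through.** The article states no sample size, event count or power, so there is no figure of its own to reproduce. The only numerical input from the document is the 0.15 level (sidedness not stated, two-sided assumed). Everything else below is an assumption.

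**Step 1: chance that a real confounder fails the screen.** For a binary confounder with prevalence 20%, z = ln(HR) × √(events × 0.2 × 0.8). The two-sided 0.15 critical value is 1.440. P(dropped) = 1 − [P(Z > 1.440 − z) + P(Z < −1.440 − z)].

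At 100 events and HR 1.5, z = 0.405 × √16 = 1.62 and P(dropped) = 0.43. At HR 1.3, z = 0.262 × 4 = 1.05 and P(dropped) = 0.65.

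| Events | HR 1.5 | HR 1.3 |
|---|---|---|
| 30 | 0.70 | 0.78 |
| 50 | 0.61 | 0.74 |
| 100 | 0.43 | 0.65 |
| 200 | 0.20 | 0.48 |
| 500 | 0.01 | 0.18 |
| 900 | <0.001 | 0.04 |

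Prevalence matters. At 100 events and HR 1.3, the chance of passing is 26% at 10% prevalence and 41% at 30%. At 1000 events it is 85% and 99%.

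**Step 2: effect on the treatment HR.** Dropping a covariate is not the same as bias, so Cox models were simulated. The true treatment HR was 1.0, with five real confounders and five noise covariates. Confounder effects were 0.15 or 0.25 on the log-HR scale per SD, and 0.3 on the log-odds of treatment per SD. The second step was assumed to be backward elimination at p<0.05. There were 600 runs per setting (150 at about 900 events).

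| Events (log-HR per SD) | Dropped: screen / both steps | Bias: full / both steps | SE/SD: full / both steps | Coverage: full / both steps |
|---|---|---|---|---|
| 40 (0.15) | 68% / 85% | 0.008 / 0.134 | 0.965 / 0.944 | 95.5% / 94.0% |
| 44 (0.25) | 42% / 64% | 0.007 / 0.152 | 0.984 / 0.932 | 95.8% / 92.7% |
| 94 (0.15) | 49% / 71% | −0.001 / 0.098 | 0.995 / 0.949 | 95.7% / 91.3% |
| 100 (0.25) | 16% / 32% | 0.001 / 0.065 | 1.005 / 0.938 | 94.5% / 93.7% |
| 199 (0.15) | 26% / 47% | 0.004 / 0.062 | 0.962 / 0.903 | 94.7% / 91.8% |
| 216 (0.25) | 2% / 5% | 0.002 / 0.009 | 0.968 / 0.942 | 93.3% / 92.2% |
| 870 (0.15) | 0.5% / 2% | 0.009 / 0.010 | 0.981 / 0.969 | 94.7% / 94.0% |
| 932 (0.25) | 0% / 0% | 0.011 / 0.010 | 0.958 / 0.958 | 92.7% / 92.7% |

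Bias is on the log-HR scale; SE/SD is the mean model standard error over the empirical SD of the estimates. The Monte Carlo error of a coverage near 95% is √(0.95 × 0.05/600) = 0.9 percentage points with 600 runs and √(0.95 × 0.05/150) = 1.8 with 150.

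**Step 3: reading the results.** At 94 events, the bias of 0.098 is an HR of exp(0.098) = 1.10 where the truth is 1.0. With the screen alone, SE/SD stays between 0.97 and 1.02 up to about 215 events, so the 0.15 rule by itself hardly narrows the intervals. The narrowing comes mainly from the second step, and part of the coverage loss is bias. Near 900 events the selection makes almost no difference.

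**The case against.** The strongest defence is propensity score matching, which the Data analysis plan and Limitations sections make the lead strategy against selection bias. Nothing applies the 0.15 screen to the propensity score. A variable strongly tied to drug choice is what such a score is meant to balance. This stands as mitigation. It does not settle the matter, because the HRs are still taken from multivariate Cox models whose covariates are selected.

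The second defence is size. The study covers a region of 8.4 million inhabitants over nine years, the effectiveness composite includes all-cause death, and intracranial haemorrhage is pooled with gastrointestinal haemorrhage in one safety composite. With many hundreds of events the problem all but disappears. That also stands, but no count is given for any of the five comparisons.

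Third, one omitted confounder may shift the HR very little. With assumed prevalences of 25% and 15% in the two groups and HR 1.3, the shift is ln(1.075/1.045) = 0.028. The SE at 50 events with equal groups is about 2/√50 = 0.28, ten times as large. This is correct for a single variable; the simulation shows that several omissions add up.

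Stronger readings are tempting, and the document does not support them:

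- A reader might infer that the warfarin, edoxaban or intracranial haemorrhage results will be badly confounded. The Introduction calls acenocoumarol the usual VKA in Spain, and the Limitations section says apixaban and edoxaban were marketed last. Smaller cohorts are thus plausible, but no size is stated.
- A reader might infer that the 0.15 rule makes the intervals clearly too narrow. The calculation shows a modest effect, arising mainly in a second step whose criterion is not given.
- A reader might infer that each drug comparison will have its own adjustment set. The article does not say whether the screen runs within each pair or on the pooled data, and different sets for thromboembolic and bleeding outcomes can be legitimate.

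**Conclusion.** The point holds in conditional form and should be acted on. The article states an inferior selection rule for the models that yield the treatment HRs, and its sentence on known confounders contains no retention rule to override it.

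Under the assumptions above, the screen alone drops a real confounder about 43% to 65% of the time at 100 events (20% prevalence, HR 1.5 to 1.3). Under the simulation's assumptions, both steps together leave a log-HR bias of 0.01 to 0.15 at about 40 to 216 events, with coverage of about 91% to 94% against 93% to 96% for a prespecified model. Near 900 events the two are practically the same.

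Omitted confounding is the larger harm and interval under-coverage the smaller. The simulation does not include matching, which would reduce these figures if the score contains all the confounders. The smaller cohorts and the bleeding endpoint, limited to haemorrhages leading to admission, are where the harm is most plausible.

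**What to change.** For the treatment-effect models, delete the 0.15 screen and the selection of a final model. Prespecify from prior knowledge one confounder set per composite outcome, use it for all five comparisons with acenocoumarol, and keep it whatever the p-values.

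Do not simply force in every variable on the article's list. CHA2DS2-VASc and HAS-BLED are built from age, comorbidities, previous events and medication (Outcome measures section), so include either the scores or their components. Where events are few, adjust through the propensity score or fit a penalised model instead of selecting by p-value. Univariate results can stay as description.

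The cost is a rewording, the work of agreeing the two sets before analysis, and slightly wider intervals in small cohorts. With large event counts almost nothing changes.
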